## Number of Participants

The total number of participants is estimated to be approximately 140 - 200.

**Part 1 Dose Escalation:** Approximately 70 participants will be enrolled in Part 1 including 25 to 30 participants in Part 1A, 6 to 9 participants in Part 1B, [REDACTED]

The actual number of participants enrolled will depend on the tolerability of PF-07248144 and the number of dose levels required to identify the MTD/RDE as a monotherapy or in combination.

**Part 2: Dose Expansion:** Approximately 90 -120 participants are expected to be enrolled in Part 2. Approximately 30 participants each will be enrolled in Parts 2A, 2B, [REDACTED] with up to an additional approximately 30 patients at an alternative dose(s).

All participants will undergo up to 28 days of screening prior to study entry. Eligible participants will then receive study intervention for up to 2 years, or until disease progression, unacceptable toxicities, a decision by the participant (withdrawal of consent or no longer willing to participate) or investigator to discontinue treatment, or study termination. Any additional treatment beyond 2 years shall be discussed and approved by the sponsor. After EOT, all participants will complete a 28 day post-treatment follow up visit for AEs. Participants in Part 2 dose expansion cohorts will be contacted by telephone approximately every 3 months for survival data collection until end of trial (2 years from last participant first dose), unless otherwise notified by the sponsor. During treatment with study intervention, all cycles will be 28 days in length.

Sample size determination is presented in [Section 9.2](#).

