| Pharmacodynamics blood
and other biomarker
sampling                                                                                                                   | See PK, Biomarker, and ECG table below.              |                                                                                                       |       |        |        |                      |        |                               |           |                  |                                                                           |
| Pfizer Prep D1 Banked
Biospecimen(s)                                                                                                                                     | See PK, Biomarker, and ECG table below.              |                                                                                                       |       |        |        |                      |        |                               |           |                  |                                                                           |

- a) **Screening:** To be obtained within 28 days prior to C1D1.
- b) **EOT Visit:** Visit to be performed as soon as possible after the last dose of study intervention and prior to initiation of any new anti-tumor therapy. Obtain assessments if not completed in the last week on study (or within 6 weeks for tumor assessments).
- c) **Post-Treatment Follow up:** At least 28 calendar days, and no more than 35 calendar days after discontinuation of study intervention, participants will return to undergo review of concomitant treatments, vital signs, and assessment for resolution of any treatment-related AEs. Participants continuing to experience treatment-related toxicity after the Post Treatment Follow-up Visit will continue to be followed at least every 28 days until resolution or determination, in the clinical judgment of the investigator, that no further improvement is expected; these may be conducted via telephone.
- d) **Informed Consent:** Must be obtained prior to undergoing any study-specific procedures. In Japan, after completion of Cycle 1, participants will be asked to sign an additional consent document for confirmation of the participant's willingness to continue participation in this study before starting Cycle 2.

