### **7. DISCONTINUATION OF STUDY INTERVENTION AND PARTICIPANT DISCONTINUATION/WITHDRAWAL**

#### **7.1. Discontinuation of Study Intervention**

In rare instances, it may be necessary for a participant to permanently discontinue study intervention (definitive discontinuation). Reasons for definitive discontinuation of study intervention may include the following:

- Objective disease progression;
- Global deterioration of health status requiring discontinuation;
- Unacceptable toxicity;
- Pregnancy;
- Significant protocol violation;
- Lost to follow-up;
- Participant refused further treatment;
- Study terminated by sponsor;

- Death;

Note that discontinuation of study intervention does not represent withdrawal from the study. If study intervention is definitively discontinued, the participant will remain in the study to be evaluated for safety follow-up and survival (Part 2 dose expansion). See the [SoA](#) for data to be collected at the time of discontinuation of study intervention and follow-up for any further evaluations that need to be completed.

In the event of discontinuation of study intervention, it must be documented on the appropriate CRF/in the medical records whether the participant is discontinuing further receipt of study intervention or also from study procedures, posttreatment study follow-up, and/or future collection of additional information.

See [Appendix 13 \(Section 10.13.3.4\)](#) for guidance for participants with active or presumed SARS-CoV2 infection.

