**9.4.2. Efficacy Analysis**

Response Evaluable Set will be used for all response related analyses including BOR, DOR, CBR, PFS, TTP and OS.

Tumor response will be presented in the form of participant data listings that include, but are not limited to tumor type, dose on Day 1, tumor response at each visit, clinical benefit response and best overall response. Proportion of participants responding to the treatment will be presented for each dose level.

For prostate cancer only, PSA and bone scan monitor, report and analysis should follow PCWG3 guidelines. Existing or new bone lesions as assessed by radionuclide bone scan will be described and documented.

PSA data will be presented in form of listings that include dose on Day 1, measurement, and % change from baseline at visit.

Part 1A, Part 1B, [REDACTED] Progression date, date of first response, last tumor assessment date, and date of last contact will be listed.

Part 2: The Kaplan-Meier methods will be used to analyze all time to event endpoints. Median PFS (if reached) will be calculated. DOR will be listed. Details of these endpoint analyses methods will be included in the SAP. Efficacy data of participants from Part 1A, Part 1B, [REDACTED] treated at the dose level selected for the corresponding expansion cohort and satisfying inclusion/exclusion criteria might be included in the analysis of efficacy endpoints of Part 2.

PFS is defined as the time from start date to date of first documentation of progression, or death due to any cause. Progression is defined as the appearance of local, regional or distant disease of the same type after complete response or progression of pre-existing lesions. It does not include second primary malignancies of unrelated types.

TTP - defined as the time from date of first dose to the date of the first documentation of PD.

OS is defined as the time from start date to date of death due to any cause.

CBR - defined as the proportion of patients with a best overall response (BOR) of CR, PR or SD lasting for 24 weeks.

The definition of each response category is provided in [Appendix 11 \(Section 10.11\)](#) (RECIST v1.1).

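### Section 9.4.2 lets Part 1 participants be pooled into Part 2 overall survival although Part 1 has no survival follow-up, so any pooled OS estimate would be biased upward (minor)

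*Protocol*

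**What the plan says.** Protocol section 9.4.2 counts OS among the efficacy analyses: "Response Evaluable Set will be used for all response related analyses including BOR, DOR, CBR, PFS, TTP and OS". It defines the endpoint ("OS is defined as the time from start date to date of death due to any cause") and names the method: "Part 2: The Kaplan-Meier methods will be used to analyze all time to event endpoints". It then states that data from Part 1 participants given a "dose level selected for the corresponding expansion cohort and satisfying inclusion/exclusion criteria might be included in the analysis of efficacy endpoints of Part 2". No endpoint is excepted. Section 3 lists OS as a secondary endpoint for Part 2. For Part 1 it does not appear among the visible endpoints, even as exploratory.

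Survival follow-up is tied to Part 2. The Synopsis says: "Participants in Part 2 dose expansion cohorts will be contacted by telephone approximately every 3 months for survival data collection until end of trial". Section 7.1 says that a participant who stops treatment stays in the study to be "evaluated for safety follow-up and survival (Part 2 dose expansion"). Table 3 (Part 2) has a survival row and a long-term follow-up column; Table 1 (Part 1) has neither. The last scheduled Part 1 visit, in footnote c of Table 1, falls "At least 28 calendar days, and no more than 35 calendar days after discontinuation of study intervention". Later contact is required only for unresolved treatment-related toxicity.

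The SAP does not close the gap. Section 5.4 repeats the pooling permission without excepting OS, and it censors participants last known alive at the date of last contact.

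**The concern.** Unobserved deaths alone do not bias a Kaplan-Meier curve, because a censored participant is not counted as a survivor. The trouble is when and why the censoring happens. Study treatment continues until progression, unacceptable toxicity or refusal, so most participants stop at progression. A pooled Part 1 participant would be at risk in the OS analysis while on treatment, when death is uncommon, and would leave the risk set about a month after stopping, just as the hazard rises. The Part 1 participants still at risk at any later time are mainly those who have not progressed. Kaplan-Meier assumes that those censored have the same future risk as those who remain, and here they do not. The pooled hazard comes out too low and the curve too high.

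What is at stake is a descriptive secondary estimate in an uncontrolled study, where any OS figure will be read against outside experience and an upward shift flatters the drug. Response, PFS and TTP are much less exposed: both schedules scan every 8 weeks for the first 48 weeks and every 12 weeks after that, although only Table 3 caps CT/MRI at 2 years.

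**Working it through.** The documents give no OS figure, event count or precision target, so there is nothing to reproduce. The check has three steps.

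**1. How many could be pooled.** Protocol section 2.2.4 (cutoff 12 September 2022) reports 4 participants at 5 mg QD in Part 1A, 4 at 5 mg QD plus fulvestrant in Part 1B, and 33 in Part 2A. Section 9.2 plans 6 to 9 in Part 1B and about 30 in Part 2B. Three Part 1 shares follow:
- Part 2A with four pooled: 4/(33+4) = 4/37 = 11%
- Part 2B with four pooled: 4/(30+4) = 4/34 = 12%
- Part 2B with all nine of Part 1B pooled: 9/(30+9) = 9/39 = 23%

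**2. Size of the bias.** A large-sample simulation (400,000 participants per scenario) compared Kaplan-Meier OS in Part 2 alone with the pooled estimate. Part 2 was followed for 24 to 36 months. Part 1 was censored 28 days after end of treatment, taken as progression. These inputs are assumptions, not document figures:
- exponential time to progression, median 4, 7 or 10 months
- exponential survival after progression, median 8, 12 or 20 months
- rare death before progression (constant hazard, mean 240 months)

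The last three columns give 24-month OS as Part 2 only → pooled. The third column comes from the 4/34 runs.

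| Median to progression | Median after progression | Share of Part 1 deaths by 24 months observed | 4/37 | 4/34 | 9/39 |
|---|---|---|---|---|---|
| 4 | 8 | 0.125 | 0.226→0.233 | 0.227→0.234 | 0.227→0.244 |
| 4 | 12 | 0.113 | 0.356→0.363 | 0.355→0.362 | 0.355→0.370 |
| 4 | 20 | 0.111 | 0.525→0.530 | 0.525→0.530 | 0.525→0.536 |
| 7 | 8 | 0.155 | 0.329→0.343 | 0.328→0.344 | 0.330→0.363 |
| 7 | 12 | 0.145 | 0.446→0.458 | 0.447→0.460 | 0.446→0.474 |
| 7 | 20 | 0.155 | 0.592→0.601 | 0.592→0.601 | 0.592→0.611 |
| 10 | 8 | 0.188 | 0.415→0.433 | 0.416→0.436 | 0.414→0.456 |
| 10 | 12 | 0.182 | 0.517→0.532 | 0.518→0.534 | 0.517→0.550 |
| 10 | 20 | 0.199 | 0.642→0.652 | 0.643→0.654 | 0.643→0.666 |

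- Observed deaths: 11 to 20% of Part 1 deaths within 24 months, so about 80 to 89% are missed.
- 24-month OS rises by 0.5 to 2.0 points with four pooled and by 1.1 to 4.2 points with nine.
- Median OS rises by 0.3 to 1.0 month with four pooled and by 0.7 to 2.6 months with nine.
- Part 1 alone would show 24-month OS of 0.68 to 0.87, against about 0.23 to 0.64 with full follow-up. The distortion within Part 1 is large; its small share dilutes it.

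**3. Against sampling error.** With at least 24 months of follow-up, SE ≈ √(S(1−S)/n). For S = 0.416 and n = 34, √(0.416 × 0.584 / 34) = 0.085. The largest four-participant shift, 0.436 − 0.416 = 0.020, is 0.020/0.085 = 0.24 of a standard error. For nine pooled, √(0.414 × 0.586 / 39) = 0.079 and 0.042/0.079 = 0.53.

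**The case against.** **Pooling is only permitted.** The protocol says such data might be included, and SAP sections 5.4 and 5.6 make separate Part 1 and Part 2 summaries the default. A reader might infer that the trial's planned OS estimate is overstated by construction. The documents do not support that: the bias attaches only to an optional pooled analysis, and a Part 2-only estimate is expected as well. This stands.

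**Fewer than four may qualify.** Part 2A takes ER+HER2- breast cancer only. Of the 21 Part 1A participants, 9 had that diagnosis, and the tumour types of the four at 5 mg are not given. If they mirrored the whole group, 4 × 9/21 = 1.7 would be eligible; the chance that all four are is C(9,4)/C(21,4) = 126/5985 = 2%. Part 2B caps prior systemic lines at three, while Part 1B states no cap. Nine from Part 1B is an upper bound: four had been treated at the cutoff, when the combination dose was already chosen. This stands too.

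**Little hangs on it.** There is no hypothesis test, Part 2 is sized on tumour response, and no rule uses OS. This stands and sets the severity.

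**Some later contact exists.** Treatment may continue while benefit persists (section 7.1.1), unresolved treatment-related toxicity is followed, and SAP section 5.7.5.1 takes last contact from many database dates. This narrows the gap but does not close it, because none of it is scheduled survival follow-up. A reader might also infer that virtually every Part 1 death would be lost. That goes too far: the simulated figure is 80 to 89%, and it depends on the assumed survival times.

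**Conclusion.** The point holds as a minor one. The pooling sentence reaches OS, and the visit schedule does not collect survival in Part 1 beyond the post-treatment visit. An analysis plan cannot recover data that were never scheduled for collection. The direction follows from the design, provided most participants stop at progression and the risk of death rises afterwards; every simulated scenario moved upward. The size rests on the assumed progression and survival times and on how many Part 1 participants are eligible. Expect roughly 0.5 to 2 points of 24-month OS with up to four pooled, and 1 to 4 points if nine came from Part 1B. Both are well inside sampling error. The reason to act is that the error is systematic, favourable and cheap to remove.

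**What to change.** In protocol section 9.4.2, and in the matching sentence of SAP section 5.4, state that Part 1 participants treated at the expansion dose and meeting eligibility might be included in the analysis of Part 2 efficacy endpoints other than OS, and that OS uses participants enrolled in Part 2 only. Pooling for response, CBR, PFS and TTP can stay as it is.

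The cost is one clause and a few participants fewer in the OS estimate: at most four per cohort on the September 2022 counts, or nine if Part 1B filled at the selected dose. No visit, assessment or sample size changes. If the sponsor wants those participants in OS, the alternative is to add the Table 3 survival call to Table 1 for Part 1 participants at an expansion dose, and to pool OS only where that contact was made. On current counts that is quarterly calls to about 4 + 4 = 8 people.

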**Table 1. Schedule of Activities: Dose Escalation (Parts 1A, 1B, 1C and 1D)**

|                                                                                                                                                                             |                                                                      | Cycle 1
(28 days)                                                                                  |       |        |        | Cycle 2
(28 days) |        | Cycles 3+,
(every 28 days) |           |                  |                                                                           |
|-----------------------------------------------------------------------------------------------------------------------------------------------------------------------------|----------------------------------------------------------------------|-------------------------------------------------------------------------------------------------------|-------|--------|--------|----------------------|--------|-------------------------------|-----------|------------------|---------------------------------------------------------------------------|
| Visit Identifier                                                                                                                                                            | Screening
(≤28 days
prior to
Cycle 1,
Day1) a | Day 1                                                                                                 | Day 8 | Day 15 | Day 22 | Day 1                | Day 15 | Day 1                         | Day
15 | EOT b | Post-
Treatment
Follow-up
(28 days
after
EOT) c |
| Tumor assessments
CT/MRI Scans of chest,
abdomen, pelvis, any
clinically indicated sites of
disease; clinical evaluation
of superficial disease t | X                                                                    | Performed every 8 weeks (±7 days) from C1D1 for the first 48 weeks and then every 12 weeks (±7 days). |       |        |        |                      |        |                               |           | X                |                                                                           |

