|-------------------------------------------------------------------------------------------------------------------------------------------------------------------------------------------------------------------------------------------------------------------------------------------------------------------------------|----------------------------------------------------------------------------------------------------------------------------------------------------------------------------------------------------------------------------------------------------------------------------------------------------------------------------------------------------------------------------------------------------------------------------------------------------------------------------------------|
| Secondary Objectives:                                                                                                                                                                                                                                                                                                  | Secondary Endpoints:                                                                                                                                                                                                                                                                                                                                                                                                                                                            |
| 
 
To evaluate antitumor activity of PF-07248144 monotherapy and in combination with fulvestrant (Part 2B) [REDACTED]
 
                                                                                                                                                          | 
 
BOR, DOR, and CBR as assessed by investigator based on RECIST v1.1.
 
PFS as assessed by investigator based on RECIST v1.1.
 
TTP as assessed by investigator based on RECIST v1.1.
 
Overall Survival.
 
                                                                                                                                                                                                         |

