## New Lesions

The appearance of any new unequivocal malignant lesion indicates PD. If a new lesion is equivocal, for example due to its small size, continued assessment will clarify the etiology. If repeat assessments confirm the lesion, then progression should be recorded on the date of the initial assessment. A lesion identified in an area not previously scanned will be considered a new lesion.

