- Unconfirmed CR (uCR) is defined as one objective status of CR documented before PD, while confirmed CR requires two objective statuses of CR a minimum of four weeks apart documented before PD. Sequences of CR - Non-evaluable - CR are considered confirmed CR as long as the two CR responses are observed at a minimum of 4 weeks apart. Similarly, unconfirmed PR (uPR) is defined as one objective status of PR documented before PD but not qualifying as uCR. Confirmed PR is defined as two objective statuses of PR or better (PR followed by PR or PR followed by CR) a minimum of four weeks apart documented before PD, but not qualifying as CR. Sequences of PR - Stable Disease or Non-evaluable - PR are considered PRs as long as the two PR responses are observed at a minimum of 4 weeks apart. Based on these definitions, the unconfirmed ORR analysis will include both confirmed CR or PR and unconfirmed CR or PR as responders, whereas the confirmed ORR analysis will only include confirmed CR or PR as responders.

Descriptive statistics (frequency and percentage) and 95% confidence interval will be provided.

2. DOR is defined as the time from first documentation of CR or PR to date of first documentation of PD or death due to any cause. The responders who have not disease progressed at the time of analysis will be censored at the last available tumor scan date. Both confirmed DOR and unconfirmed DOR (uDOR) will be determined separately for the subset of participants with a confirmed and unconfirmed objective response of CR or PR.
3. *CBR is defined as the proportion of patients with a best overall response (BOR) of CR, PR or SD lasting for 24 weeks.*

4. *PFS is defined as the time from start date to date of first documentation of progression as per RECIST 1.1, or death due to any cause. Progression is defined as the appearance of local, regional or distant disease of the same type after complete response or progression of pre-existing lesions. It does not include second primary malignancies of unrelated types.*

PFS will be summarized using the Kaplan-Meier method, as described in [Section 4.3.4](#), and may also be displayed graphically when appropriate.

5. TTP is the time from start date to the date of the first documentation of PD per RECIST 1.1. Start date is the start of treatment.

TTP will be summarized using the Kaplan-Meier method, as described in [Section 4.3.4](#). TTP may also be displayed graphically when appropriate.

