## 8. APPENDICES

### 8.1. Appendix 1: Time to Event Data Analysis Censoring Rules

**Table 2. Progression Free Survival Outcome and Event Dates**

| Situation                                                                                                                                                                                                                                               | Date of Event/Censoring                                                                                                            | Outcome               |
|---------------------------------------------------------------------------------------------------------------------------------------------------------------------------------------------------------------------------------------------------------|------------------------------------------------------------------------------------------------------------------------------------|-----------------------|
| No adequate baseline assessment                                                                                                                                                                                                                         | ‘start date’ a                                                                                                          | Censored a |
| PD or death 

- after at most one missing or inadequate post-baseline tumor assessment, or

- ≤ 17 weeks after ‘start date’.

                                                                       | Date of PD or death                                                                                                                | Event                 |
| PD or death 

- after 2 or more missing or inadequate tumor assessments (> 17 weeks) .

                                                                                                                 | Date of last adequate tumor assessment b documenting no PD prior to new anti-cancer therapy or missed tumor assessments | Censored              |

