**Table 3. Titime to Progression Outcome and Event Dates**

| Situation                                                                                                                                                                                                                                | Date of Progression/Censoring                                                                                                       | Outcome  |
|------------------------------------------------------------------------------------------------------------------------------------------------------------------------------------------------------------------------------------------|-------------------------------------------------------------------------------------------------------------------------------------|----------|
| No adequate baseline assessment                                                                                                                                                                                                          | ‘start date’                                                                                                                        | Censored |
| PD
- after at most one missing or inadequate post-baseline tumor assessment, or
- ≤ 17 weeks after ‘start date’.                                                                                                                   | Date of PD                                                                                                                          | Event    |
| PD
- after 2 or more missing or inadequate tumor assessments (> 17 weeks). a                                                                                                                                               | Date of last adequate tumor assessment a documenting no PD prior to new anti-cancer therapy or missed tumor assessments. | Censored |
| No PD                                                                                                                                                                                                                                    |                                                                                                                                     |          |

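### The PFS progression wording contradicts RECIST v1.1 on new lesions; separately, the missed-scan count and the 17-week figure in the censoring rule disagree once scans are 12-weekly

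*Protocol*

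**What the plan says.** **Progression.** Protocol Section 3 sets the endpoint as "PFS as assessed by investigator based on RECIST v1.1": secondary in Part 2, exploratory in Part 1. Section 9.4.2 then adds its own definition: "Progression is defined as the appearance of local, regional or distant disease of the same type after complete response or progression of pre-existing lesions". SAP 5.4 describes the event as "date of first documentation of progression as per RECIST 1.1, or death due to any cause" and follows it with the same narrower sentence. Protocol Appendix 11 states, under New Lesions: "The appearance of any new unequivocal malignant lesion indicates PD". Its objective-status table gives PD whenever a new lesion is present, whatever the target and non-target status. TTP carries no narrower definition: "TTP - defined as the time from date of first dose to the date of the first documentation of PD".

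**Gap rule.** SAP Appendix 1, Table 2 (PFS) counts PD or death as an event if no more than one post-baseline assessment was missing or inadequate, or if it falls within 17 weeks of the start date. It censors PD or death "after 2 or more missing or inadequate tumor assessments", with more than 17 weeks in brackets. Table 3 applies the same pair of rules to TTP. Footnotes to both tables speak of elapsed time without an adequate assessment.

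**Scan schedule.** In Part 1, tumor assessments are "Performed every 8 weeks (±7 days) from C1D1 for the first 48 weeks and then every 12 weeks (±7 days"). The Part 2 schedule makes the same switch and runs for up to 2 years.

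**The concern.** An endpoint needs one definition of its event. A new metastasis in a participant with stable disease or partial response is neither disease after complete response nor progression of a lesion already present, so the sentence in 9.4.2 does not cover it. RECIST does. If an analyst followed the sentence literally, PFS would miss those progressions and the Kaplan-Meier estimate would be too high. With no control arm, a comparison could not offset that bias.

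The censoring rule has a similar problem. It gives two tests, a count and a time, that are meant to be the same test. When they part, the same PD can be an event or a censored observation depending on which test the programmer uses.

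**Working it through.** **1. The two definitions of progression, applied to one case.** Take a participant with partial response, no prior CR, and a new unequivocal liver lesion.

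- Appendix 11 (New Lesions and the status table): PD.
- TTP in 9.4.2: event at that date, since it takes any first PD.
- PFS sentence in 9.4.2 and SAP 5.4, read literally: no event, because there was no CR and no existing lesion progressed.

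PFS counts progression or death, so it can never be later than TTP. Under the literal sentence it could be. If the participant then starts new therapy, SAP Table 2 would censor PFS at the last adequate assessment, while TTP has its event at the PD date. That incoherence shows the sentence is wrong as written.

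**2. Where 17 weeks comes from.** Two 8-week intervals plus a one-week window: 2 × 8 + 1 = 17. The figure is reproduced, but from the 8-weekly phase only.

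**3. Gaps on the protocol schedule.** Nominal scans fall at weeks 0, 8, 16, 24, 32, 40, 48, 60, 72, 84 and 96. Each visit has ±1 week, so a gap between two on-study scans varies by ±2 weeks, and a gap from the start date by ±1.

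| Missed scans | Last scan → next scan (weeks) | Nominal gap | With windows | By count | Over 17 weeks? |
|---|---|---|---|---|---|
| One, from start | 0 → 16 | 16 | 15-17 | event | no |
| One, 8-weekly phase | e.g. 8 → 24 | 16 | 14-18 | event | no nominally; yes at the extreme |
| One, week-48 scan | 40 → 60 | 20 | 18-22 | event | yes |
| One, 12-weekly phase | e.g. 48 → 72 | 24 | 22-26 | event | yes |
| Two, 8-weekly phase | e.g. 8 → 32 | 24 | 22-26 | censored | yes |
| Two, 12-weekly phase | e.g. 48 → 84 | 36 | 34-38 | censored | yes |

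The tests agree nominally until the gap reaches past week 48. From then on, every single missed scan splits them.

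**4. Illustrative size of the gap rule if time is the operative test.** All inputs here are assumptions: exponential PFS with median 4 to 12 months, independent per-scan miss rate m of 5% to 15%, and follow-up to week 96 at nominal scan times. With one missed scan between two attended scans, the gap exceeds 17 weeks for 40 → 60, 48 → 72, 60 → 84 and 72 → 96. The progression can fall before or after the missed scan, so

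P(affected) = m(1 − m)² × {[S(40) − S(84)] + [S(48) − S(96)]}, and the share of progressions = P(affected) / [1 − S(96)].

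Example: median 6 months = 26 weeks, m = 0.10. S(40) = 0.344, S(48) = 0.278, S(84) = 0.107, S(96) = 0.077. P = 0.10 × 0.81 × (0.237 + 0.201) = 0.0355. Share = 0.0355 / 0.923 = 3.85%, or 30 × 0.0355 = 1.07 per 30 participants.

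Across the grid, the lowest value is 1.35% (0.40 per 30; median 4 months, m = 5%). The highest is 7.65% (1.66 per 30; median 12 months, m = 15%).

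**5. Size of the new-lesion omission.** This cannot be computed. The documents give no split of first progressions into new lesions and growth of existing ones.

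**The case against.** The strongest reply is that the plan already commits to RECIST. Section 3 says so, 9.4.2 ends by referring response categories to Appendix 11, SAP 5.4 names RECIST 1.1 in the sentence just before the disputed one, and the event in SAP Table 2 is PD, the RECIST status. An experienced programmer may well follow RECIST throughout. This stands to the extent that a reader might infer from the PFS sentence that real progressions will be dropped, and the documents do not support that. They do not settle the matter the other way either: the sentence is a formal definition, more specific than the references around it, and it was carried into the SAP.

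On the gap rule, a reader might infer that PD after one missed 12-weekly scan is censored. The tables do not say that. Their event row makes PD after a single missed assessment an event, and the 17 weeks stands in brackets beside a count of two or more. Censoring follows only if the time is taken as the operative test. The footnotes' elapsed-time wording invites that reading without requiring it.

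The reach is also limited. There is no formal hypothesis testing, the Part 2 primary endpoints are adverse events and laboratory abnormalities, the Part 2 sample size reasoning in 9.2.2 uses response rate, and no decision rule uses PFS. All of that stands, and it sets the severity.

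**Conclusion.** The PFS sentence is wrong as written, because it contradicts the declared RECIST v1.1 endpoint, Appendix 11 and the PD used for TTP. Read literally, it biases PFS upward by an amount the documents do not allow anyone to state. The gap rule is undetermined for a single missed scan once the gap extends past week 48, because the count says event and the time figure says censor. This second defect affects both PFS and TTP.

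Under the time reading and the assumptions shown, roughly 1-8% of progressions are touched, or about 0.4 to 1.7 per 30-participant cohort. The share still at risk at week 48 (28%, 43% and 53% for assumed medians of 6, 9 and 12 months) should not be read as the share affected. A case must also have a missed scan next to the progression.

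The consequence is confined to descriptive Kaplan-Meier estimates, which are secondary in Part 2. Severity: moderate.

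**What to change.** 1. In protocol 9.4.2 and SAP 5.4, replace the progression sentence with: progression is PD per RECIST v1.1 (Appendix 11), including new lesions. The exclusion of unrelated second primary malignancies can stay.

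2. In SAP Tables 2 and 3, define the censoring row as PD (or death, for PFS) after two or more consecutive scheduled assessments that were missed or inadequate. Drop the bracketed 17 weeks as the gap test and align the footnotes with the count. The uses of 17 weeks measured from the start date lie within the 8-weekly phase and can remain.

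A second time limit for the later phase is less clean. The same construction gives 2 × 12 + 1 = 25 weeks, but one missed scan can reach 26 weeks with windows, and the 20-week gap around a missed week-48 scan would need its own rule. The count avoids both problems.

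Cost: two wording edits and a small programming change, with no new data. Make the changes before any PFS or TTP analysis is run.
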